The peak growth spurt is known to take place between 10 and 14 years in 95% of the girls, and between 12 and 16 years in 95% of the boys[8,9]. This range holds for a large population, but is too wide to make accurate predictions in the individual patient. However, several other maturity indicators are related to the pubertal growth spurt. Maturity is multidimensional and has various components, including chronological age, skeletal age in different areas, the Risser sign, status of the triradiate cartilage, Tanner stage of sexual maturation, age at thelarche and menarche, and several length dimensions like sitting height, subischial leg length, and foot length or shoe size. These indicators of maturity are all signs that reflect growth or remaining growth of the patient and can be useful in predicting timing of the pubertal growth spurt or peak growth velocity of total body height in the individual patient.

Researchers have tried to find different ways to predict curve progression in AIS as well, besides relating progression to the peak growth velocity of height. A promising method was shown by Cheung et al[3,10], who found a relationship between curve progression and altered electromyography ratios of the convex and concave sides of the curve. Enhanced EMG ratios were observed at three levels of the scoliotic curve (lower end vertebra, apex, and upper end vertebra) at the start of progressive periods. At the start of a non-progressive period, such an enhanced EMG ratio was only observed at the level of the apex vertebra[3].

Only few studies have investigated maturity indicators in patients with idiopathic scoliosis[11-14]. Moreover, studies have compared only some of these indicators, and only either in relationship to the peak growth velocity of total body height, or to curve progression, not to both in one study. Results of different studies are contradictory and inconsistent, so therefore a good algorithm for determining treatment options in AIS is still lacking.

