The goal of this study is to determine the predictive value of several maturity indicators that reflect growth or remaining growth potential, in order to predict timing of the peak growth velocity of total body height in the individual patient with adolescent idiopathic scoliosis. Furthermore, different parameters are evaluated for their correlation with curve progression in the individual scoliosis patient. An algorithm is made for determining the optimum treatment strategy in the individual patient with adolescent idiopathic scoliosis.

A description of the maturity indicators is presented below.

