### Skeletal age dimensions

Any skeletal region with consistent physeal markers is amenable to be a determination of skeletal age. The most commonly used markers of skeletal age in patients with idiopathic scoliosis are the hand, wrist and the ossification of the iliac apophysis (Risser sign).

Unfortunately, there is a fairly wide range of skeletal age compared with pubertal stages and pubertal growth, although the variation is less than with chronological age.

Determination of skeletal age by hand and wrist X rays is usually done by the method of Greulich and Pyle or Tanner and Whitehouse. The latter is more reliable and reproducible but also fairly complex and time consuming. The Tanner Whitehouse classification can predict well if the patient is pre- or post pubertal growth spurt. The Greulich and Pyle method of assessing skeletal age is easier to use but less precise, and the atlas was compiled from radiographs made in the 1930s [24].

The Risser sign (ossification of the iliac apophysis) continues to be an accepted prognostic sign in the evaluation of growth of patients with idiopathic scoliosis. There is, however, considerable and growing controversy[12-14,25-27]. Disadvantage of using the Risser sign is the wide distribution and the fact that it typically appears after de peak growth velocity of height. Risser stage 1 occurs after the growth spurt in 85% of patients, so its predictive value is very low.

Sanders et al[12] found the status of the triradiate cartilage to be more predictive for the timing of the peak growth velocity of total body height, though it is only predictive whether the patient is before or after the pubertal growth spurt. Once the patient had closed triradiate cartilages, he or she is very likely past the pubertal growth spurt. However, the predictive value of open triradiate cartilages is less clear.

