### Secondary sexual characteristics

Another hallmark of maturation is de development of secondary sexual characteristics, often classified by Tanner. Thelarche, the first stage of secondary breast development, marks the beginning of puberty and usually takes place 1 year before the peak growth velocity of height[4,11,29,30]. Girls typically reach peak growth velocity of height between stage 2 and 3 of breast development and pubic hair development. The pubertal or Tanner stages are good measurements of maturity. However, most orthopaedic surgeons are uncomfortable in evaluating secondary sexual characteristics with their patients, and self assessment of patients is said to be unreliable. Timing of menarche, the first menstrual period, can be used in girls, but most often takes place 1 year after PHV and is therefore always retrospective. It is assumed that the timing of menarche of the child is closely related to the timing of menarche of the mother. When the mother can recall the timing of her menarche, some predictions can be made for the timing of menarche of the child, and therefore for the timing of the pubertal growth spurt. However, it is still unknown how accurate this relationship is.

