### Identification and recruitment of study participants

Patients between 8 and 17 years old, visiting the outpatient clinic of the UMCG with adolescent idiopathic scoliosis will be participating in this study. The Cobb angle should be >10 degrees, measured by an experienced observer on an AP X-ray of the total spine.

Patients should not have had previous spinal surgery; there should be no evidence of neuromuscular disease or skeletal dysplasia, and no evident abnormalities of maturation or height. Furthermore, patients with mental incapacitation are excluded since this can influence the reliability of the measurements in the way that these patients most often can not stand still during the height measurements and EMG measurements. Patients are excluded as well when they are participating in a different study simultaneously.

The assessment to include or exclude a patient will be determined by the orthopaedic surgeon. All patients who meet the inclusion criteria will be asked to participate in this study and give their informed consent.

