### Study protocol

The study protocol will be incorporated in the usual care of patients visiting the outpatient clinic for follow up of adolescent idiopathic scoliosis. Follow up will take place every six months. Patients will be followed until 18 years of age or until growth of the spine has stopped and skeletal maturity has been reached. Furthermore, patients will be lost to follow up when they receive surgical treatment.

A description of the (follow up) consult is presented below.

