### Sample size and statistical analysis

The maximum sample size of this study is not determined on beforehand, as the study is aimed to proceed for the coming years.

We aim to perform a first preliminary analysis of the longitudinal data when patients have a follow up of at least 2 years. As the expected number of new patients is 60 each year, it will take 2.5 years for 30 patients to reach a follow up of at least 2 years. Taking a loss to follow up into account due to surgical treatment, we expect to be able to analyse the complete data of at least 25 patients. The statistical power will increase with a longer follow up and more patients. The number of 25 patients was checked whether it was large enough to obtain a good prediction model according to the criteria of Knofczynski and Mundfrom [33]. With a significant large influence of 4-5 predictor variables (as is expected in this study) and a squared multiple correlation coefficient between 0.5 and 0.7 between 25 and 65 patients should be included. Therefore the first preliminary analysis will be performed using data of 25 patients.

Individual data charts are made, and results of each parameter are plotted against the growth velocity of total body height and the curve progression.

All statistical calculations are made using SPSS (SPSS Inc, Chicago USA). Pearson correlation coefficients are computed for each individual possible related parameter against the peak growth velocity and the curve progression (Figure 5). A correlation above 0.70 is believed to be clinically relevant. To be able to interpret this value in a reliable way, we will report the confidence intervals as well.

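### The analysis of peak timing does not separate values known before the height peak from those known only after it, so late maturity signs can rate as predictors

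*Protocol article*

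**What the plan says.** The objective at the end of the Background is prospective and individual: maturity indicators are studied "in order to predict timing of the peak growth velocity of total body height in the individual patient with adolescent idiopathic scoliosis".

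The sampling frame spans the peak. Under Identification and recruitment, "Patients between 8 and 17 years old, visiting the outpatient clinic of the UMCG with adolescent idiopathic scoliosis will be participating in this study", with no requirement that the peak is still ahead. Under Study protocol, "Follow up will take place every six months" and "Patients will be followed until 18 years of age or until growth of the spine has stopped and skeletal maturity has been reached". The Background states that "The peak growth spurt is known to take place between 10 and 14 years in 95% of the girls", and places the peak of boys at 12 to 16 years.

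Under Sample size and statistical analysis, "Pearson correlation coefficients are computed for each individual possible related parameter against the peak growth velocity and the curve progression", and a correlation above 0.70 counts as clinically relevant. The same section then names multiple linear regression to derive equations for the timing and size of the peak. The Abstract (Methods/design) confirms that the correlations are meant to relate to the timing of the spurt. No sentence fixes the visit from which a predictor value is taken.

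The background sections describe three indicators as late signs:

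- Menarche "most often takes place 1 year after PHV and is therefore always retrospective".
- "Risser stage 1 occurs after the growth spurt in 85% of patients, so its predictive value is very low".
- Closed triradiate cartilage means that the child is very probably past the spurt, while the meaning of open cartilage is described as less clear.

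All three are still collected and fall under the rule that every parameter is tested.

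**The concern.** A forecast of when the peak will come can use only what is known before it comes. A sign that appears after the peak may track its timing closely and still be useless to a clinician whose patient has not reached it. The stated test (every parameter, one correlation bar, one set of regression equations) cannot tell the two kinds of indicator apart. The Discussion declines blood serology partly because most such parameters are conclusive only in retrospect, but the analysis has no matching safeguard for the indicators it keeps.

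Two things are at stake. The Abstract and the Discussion offer the separate correlations so that clinicians can choose which indicators suit their practice, and late signs could look attractive there. Early indicators such as thelarche, distal segment growth and elbow age would also be ranked against competitors whose correlations arise largely from visits at which no peak remains to be predicted.

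**Working it through.** **The plan's own figures.** The protocol gives no number on this point. Its count for the first analysis reproduces: 60 per year × (2.5 − 2.0) years = 30, and 25 of 30 implies a loss of 5/30 = 16.7%. At n = 25 an observed r of 0.70 has a 95% interval of 0.42 to 0.86 (Fisher z, half-width 1.96/√22). That interval describes sampling error and does not show whether the value was known in time.

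**Inputs from the document.** Peak at 10 to 14 years in 95% of girls; Risser 1 after the peak in 85%; menarche about 1 year after the peak; visits every six months; entry at 8 to 17 years.

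**Assumptions.** Normal distributions; SD of the lag from peak to sign 0.5 to 1.0 years; Risser stages 0.5 to 0.75 years apart; visits spread evenly around the peak.

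**Check 1: one value per patient, no pooling of visits.** SD of age at peak in girls = 4/(2 × 1.96) = 1.02 years. If age at menarche = age at peak + an independent lag with SD s, then r = 1.02/√(1.02² + s²).

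| s (years) | r, age at menarche with age at peak |
|---|---|
| 0.5 | 0.90 |
| 0.75 | 0.81 |
| 1.0 | 0.71 |
| 1.25 | 0.63 |

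The bar of 0.70 is passed when s is below 1.02 × √(1/0.49 − 1) = 1.04 years, although the value is known only after the event.

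**Check 2: visit-level values.** Time of Risser 1 after the peak ~ N(1.036 × s, s), so that 85% fall after it. Menarche is yes/no at each visit, with mean lag 1 year. Correlation is with time relative to the peak (400,000 simulated visits per setting).

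| Visits (years from peak) | s | Risser, all visits | Risser, pre-peak | Menarche, all visits | Menarche, pre-peak |
|---|---|---|---|---|---|
| −2 to +2 | 0.5 | 0.75–0.76 | 0.19 | 0.69 | 0.07 |
| −2 to +2 | 0.7 | 0.66–0.67 | 0.19 | 0.65 | 0.14 |
| −2 to +2 | 1.0 | 0.54–0.55 | 0.18–0.19 | 0.59 | 0.20 |
| −2 to +3 | 0.5 | 0.86–0.87 | 0.19 | 0.81 | 0.07 |
| −2 to +3 | 0.7 | 0.80 | 0.19–0.20 | 0.78 | 0.14 |
| −2 to +3 | 1.0 | 0.69–0.70 | 0.18–0.19 | 0.71 | 0.20 |

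Ranges within a cell cover the two stage spacings. At 96 to 98% of pre-peak visits Risser 1 has not yet appeared, so the indicator hardly varies there.

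**Check 3: a different visit pattern.** Girls enter evenly over ages 8–17, 10–14 or 10–15 and are seen six-monthly for 2 years or until 4 years after the peak (at most to age 18), with s of 0.5 or 1.0 and Risser stages 0.5 years apart. Between 50 and 60% are past the peak at the first visit, and 67 to 84% of visits are post-peak. In absolute value, Risser correlates 0.76 to 0.90 over all visits and 0.14 to 0.16 before the peak; menarche status 0.70 to 0.83 and 0.05 to 0.19.

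The levels move with the assumptions. The gap between all-visit and pre-peak results appears in every setting.

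**The case against.** The strongest reply is that the article never says visits are pooled or that time to peak is the outcome. The correlation sentence names peak growth velocity, the remark about a missed visit can mean one correlation per time point across patients, the figure listing the correlations is not visible, and the choice of predictor visit is often left to a fuller document. It stands that pooling is an inference. The point does not depend on it: age at menarche, taken once per patient, passes the bar in Check 1. It is also more than an omitted detail, because the stated rule covers every parameter, including those that the background calls uninformative in advance.

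Other parts of the reply stand and limit the point:

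- A reader might infer that the protocol calls all three signs retrospective. Only menarche is so described. The 85% figure leaves 15% with Risser 1 not after the spurt, and triradiate status is said to separate before from after.
- A reader might infer that these signs are bound to pass 0.70. Several scenarios fall short.
- A reader might infer that post-peak visits should not be collected, or that the timing model should use only pre-peak visits. Post-peak visits are needed to locate the peak and are legitimate for curve progression. Selecting visits by the observed peak conditions on the outcome, and a clinician seeing a new patient does not know whether the peak has passed.

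The protocol does disclose the limits of these signs in its background. Disclosure there does not change how the stated test would rate them.

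**Conclusion.** The concern holds in a limited form. As written, the analysis of timing can credit an indicator with predictive value that comes from information available only after the peak, and the protocol itself identifies the signs most exposed to this. Under lag SDs of 0.5 to 1.0 years, age at menarche correlates 0.90 to 0.71 with age at peak. With visits spread evenly around the peak, Risser stage correlates 0.54 to 0.87 with time relative to peak over all visits, against about 0.18 to 0.20 before it.

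The size rests on assumed lag SDs, stage spacing and visit patterns; the documents give none of the first two. Triradiate status was not simulated, so for it the argument is qualitative. The documents do not establish that a late sign will clear the bar, or that it will end up in the final algorithm. They do establish that nothing in the stated analysis would reveal the difference. The point deserves correction before the first analysis.

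**What to change.** Amend the analysis wording under Sample size and statistical analysis as follows:

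1. For timing, allow as predictors only values known at the visit from which the prediction is made, for example the first visit or a fixed landmark age. Use signed time from that visit to the peak as the outcome.
2. Report each indicator's performance separately for visits before the peak, and apply the relevance bar for predicting timing to that figure.
3. Report Risser sign, triradiate status and menarche also as classifiers of whether the peak has passed (yes/no), with sensitivity and specificity.
4. Do not let a model fitted only to visits selected by the observed peak be the sole timing model.

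The cost is in wording and analysis, with no new data. Fewer visits will support the timing results, and the reported correlations for the late signs will be lower. Children already past the peak at entry may have no observed peak date, so their number should be reported.

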**Figure 2 F2:**
[figure not shown]
**Calculation of the length of the scoliotic spine as described by Cheung et al.** The length is measured from T1 to L5 through the midpoints of all vertebrae and discs.

Determination of the state of the triradiate cartilage is performed on the AP X-ray of the pelvis (open or closed), as well as determination of the Risser stage (stage 1-5).

Skeletal age of the hand and wrist is determined by a trained observer according to the method of Tanner and Whitehouse. Skeletal age of the elbow is assessed by the Sauvegrain method, using a scoring system for four anatomical landmarks of the elbow[28].

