### Outcome measurements

Longitudinal data will be acquired for:

• Scoliotic curve progression (in degrees Cobb angle)

• Height, and growth velocity of height

• Sitting height, and growth velocity of sitting height

• Leg length, and growth velocity of leg length

• Foot length, shoe size, and growth velocity of foot length and shoe size

• Weight, and growth velocity of weight

• Spinal length, and growth velocity of spinal length

• Tanner stage of secondary sexual characteristics

• Riser sign and status of the triradiate cartilage

• Skeletal age in hand, wrist, and elbow

• EMG ratios of the paraspinal muscles

Finally, an algorithm will be developed for predicting peak growth velocity of height and curve progression in individual patients with adolescent idiopathic scoliosis (see Figure 4). 

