As mentioned before, the use of a new ultra low dose X-ray system is a huge advantage of this study. However, not all clinicians will have access to a system like that, and can not determine skeletal age in many different regions, as radiation exposure will be too high for the patient. Furthermore, not all clinicians will have the time and space to perform many measurements in their outpatient clinic. Therefore correlations with peak growth velocity of total body height and curve progression are calculated for each individual parameter as well, so that researchers and clinicians can choose which parameter is interesting and feasible in their practice.

In conclusion, this study will provide an extensive and valuable database of many (growth) parameters related to the peak growth velocity of total body height and the curve progression in patients with adolescent idiopathic scoliosis. This information will be helpful in determining the optimum treatment strategy for patients with AIS and therefore in prevention of complications and improvement of the prognosis.

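### One Pearson value of 0.70 is the relevance mark for every indicator, but open/closed triradiate status, if correlated as recorded, may be unable to reach it when the split is uneven

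*Protocol article*

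**What the plan says.** Under *Sample size and statistical analysis*, the protocol article fixes the coefficient and its scope: "Pearson correlation coefficients are computed for each individual possible related parameter against the peak growth velocity and the curve progression". The relevance mark follows without any distinction by measurement scale: "A correlation above 0.70 is believed to be clinically relevant". Intervals are to be given beside the coefficients: "To be able to interpret this value in a reliable way, we will report the confidence intervals as well". No other coefficient or mark is named for two-level or staged indicators.

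The *Outcome measurements* list includes "Riser sign and status of the triradiate cartilage". The radiographic reading has two levels (*X-ray examinations*, text after Figure 2): "Determination of the state of the triradiate cartilage is performed on the AP X-ray of the pelvis (open or closed").

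The background (*Skeletal age dimensions*) reports a cited study that found this sign more predictive of peak timing than the Risser sign, but adds that "it is only predictive whether the patient is before or after the pubertal growth spurt" and that the meaning of open cartilage is less clear.

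The *Discussion* says why single-indicator correlations are reported at all: "so that researchers and clinicians can choose which parameter is interesting and feasible in their practice". The abstract makes the same offer.

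**The concern.** A two-level variable cannot correlate perfectly with a continuous outcome, even when it divides that outcome without error. Its ceiling moves with the share of children in each state and with the shape of the outcome distribution. A fixed mark of 0.70 therefore asks something different of open/closed status than of sitting height or foot length.

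At stake is the comparison that the study offers to clinicians. A sign that separates before-peak from after-peak perfectly could be read as not clinically relevant because few children in the sample were in one of the two states. Its coefficient would also stand in the same list as those of continuous measures, although the two are not on a comparable scale. Staged indicators (Risser, Tanner) share the effect in a milder form.

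**Working it through.** **The plan's own figure.** The article expects 60 new patients a year and a first analysis at 2.5 years among those with at least 2 years of follow-up. 60 × (2.5 − 2) = 30, as stated. Going from 30 to 25 implies a loss of 1 − 25/30 = 16.7%. So 25 is the sample size used below. The 0.70 is stated as a belief and has no derivation to reproduce.

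**Inputs from the article.** Pearson coefficient for each indicator; mark 0.70; triradiate status open or closed; n = 25 at the first analysis.

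**Assumptions, not in the article.** Status is correlated as recorded, one reading per child. The marker is perfect: every child in one state has a higher outcome value than every child in the other. The outcome is continuous, and its shape is varied below.

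**Step 1: ceiling.** Let p be the share in one state.

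- Normal outcome: r_max = φ(z_p) / √(p(1 − p)), where φ is the standard normal density and z_p the normal quantile.
- Uniform outcome: r_max = √(3p(1 − p)).

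Examples: at p = 0.5 the normal case gives 0.3989/0.5 = 0.798 and the uniform case √0.75 = 0.866. At p = 0.2 they give 0.2800/0.4 = 0.700 and √0.48 = 0.693.

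| Split | Normal | Uniform |
|---|---|---|
| 50/50 | 0.798 | 0.866 |
| 40/60 | 0.789 | 0.849 |
| 30/70 | 0.759 | 0.794 |
| 25/75 | 0.734 | 0.750 |
| 20/80 | 0.700 | 0.693 |
| 15/85 | 0.653 | 0.619 |
| 10/90 | 0.585 | 0.520 |

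The ceiling crosses 0.70 at p = 0.200 (normal) and p = 0.206 (uniform). For a skewed (exponential) outcome the position shifts: the ceiling is 0.69 at 50/50, 0.80 when the state with the higher values holds 20%, and 0.45 when it holds 80%. The 20% point is therefore not general.

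**Step 2: samples of 25.** The ceilings in Step 1 are population values, so a sample can land on either side. I drew samples of 25 from a normal outcome (100,000 per row) and placed the k highest values in one state.

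| k of 25 in one state | Mean r | Share with r ≤ 0.70 |
|---|---|---|
| 12 | 0.797 | 1.5% |
| 7 | 0.747 | 18% |
| 5 | 0.693 | 53% |
| 4 | 0.655 | 75% |
| 3 | 0.603 | 92% |

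**Step 3: do the intervals help?** With n = 25 and r = 0.70, the Fisher interval tanh(atanh 0.70 ± 1.96/√22) is 0.42 to 0.86. The 95% level is assumed, and the method is approximate for a two-level variable. The interval is wide, but it expresses sampling error around the capped coefficient and does not remove the cap.

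**The case against.** Several points on the other side stand.

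- **The split and the outcome distribution are not given.** Recruitment at 8 to 17 years with six-monthly visits towards maturity does not establish a lopsided split. Near an even split with a normal outcome, a perfect marker nearly always exceeds 0.70.
- **The 0.70 is a guide to reading.** Nothing makes it a test or a gate into the multiple regression, where a two-level predictor is legitimate. The analysis of 25 is preliminary.
- **A lower coefficient is partly a true answer.** The aim is to predict timing, and a before/after sign carries less timing information than a graded measure. The background presents this as a limitation. Age mix also changes the correlations of continuous measures.
- **The variable that enters the correlation is not spelled out.** Age at closure against age at peak would escape this cap. The article states no such derived variable; its figure of the correlations investigated is not shown.

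A reader might infer that the sign can never pass: an underlying correlation of 0.85 would appear as 0.85 × 0.798 = 0.68 even at 50/50. That inference fails. The 0.85 is not in the documents, 0.68 is a population value for a normal outcome, and simulation of that case at n = 25 puts the observed coefficient above 0.70 in about 45% of samples.

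None of this removes the core point. The article names the coefficient, applies it to every indicator, gives one relevance value and offers the results for choosing between indicators.

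**Conclusion.** The point holds in a conditional form. If open/closed status is correlated as recorded, 0.70 is not a fair relevance mark for it, and its coefficient is not comparable with those of the continuous indicators. For a normal outcome, a perfect marker shows 0.70 or less in 1.5% of samples of 25 at a 12/13 split, 18% at 7/18 and 53% at 5/20.

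This rests on one reading per child, a perfect marker and an assumed outcome shape. The documents support saying that the rule can mislabel a good before/after sign. They do not support saying that it will, or that every low coefficient for this sign would be an artefact.

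**What to change.** - Keep the Pearson coefficients, and the timing and curve-progression analyses, for the continuous indicators.
- State that 0.70 is not the relevance criterion for open/closed triradiate status.
- Add one table giving the sensitivity and specificity, with confidence intervals, of closed cartilage for peak height velocity already passed.
- In the same table, give the AUC of the other indicators for that target, as a supplementary common scale.

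The table should stand beside the correlations. Moving every indicator to a before/after target would drop timing, which is the study's main aim.

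The cost is a few sentences and one table, with no new data. The downside is a second summary measure to explain, one that covers before/after status only and says nothing about curve progression.
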